### Sample size

The sample size will be determined based on the priori power analysis through G*Power software version 3.1.9.2 [26]. In the calculations, ANOVA repeated measures between factor will be chosen, effect size 0.25, alpha 0.05, power 0.80, number of groups 4, number of measures 5, and the sample size is calculated as 168. Taking into account a conservative anticipation of a 20% drop-out rate, the final sample size will therefore be 53 in each group, with a total of 212 subjects.

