### Randomization, allocation concealment and blinding

The stratified randomization with gender and KL grade as factors will be used to randomly assign the eligible participants to four groups. First, the participants will be grouped by gender. Then, male and female will be grouped by KL grade. After grouping, there will be six subgroups: (1) male, KL = I; (2) male, KL = II; (3) male, KL = III; (4) female, KL = I; (5) female, KL = II; (6) female, KL = III. For any one subgroup, the participants will randomly divide into group A, B, C and D group, and all group A, B, C and D group are merged to form a new group A, B, C and D group. The randomization number lists will be generated by the random number generator of the SPSS software (Version 22.0; IBM Corp., NY, USA).

The allocation of participants will be hidden in opaque numbered and sequentially sealed envelopes, prepared by a researcher who did not participate in the recruitment and assignment of the groups. The corresponding envelopes will be opened to determine a patient’s group assignment once the participants enrolled have completed all baseline assessments. In addition, physiotherapists with same level, TC coaches and IAI operators also will be followed randomization and randomly assigned to any group.

Due to the visible nature of the exercise intervention, blinding of the study investigators and the participants for TC will be impossible [28]. To ensure blinding of the PRP and concealment of randomization, the independent laboratory pharmacist prepared a syringe with PRP and a syringe with placebo (isotonic saline: 0.9% sodium chloride) [29]. They covered study syringes with a specially manufactured thick plastic covering sheath to conceal the appearance of the study intervention. After the intra-articular injection, the syringe covered by the sheath (containing either the remnants of the PRP or saline) will be handed back to the independent research assistant, who disposed of the syringe in effort to maintain blinding of the study team. The success of blinding will be assessed by asking patients just after the injections what treatment they thought they had received. Furthermore, blinding will be applied to the outcome assessors and statisticians who conduct the final statistical analyses in this protocol to avoid potential detection bias. The outcome assessors will be responsible for data collection and analysis, and they will not be involved in the subject recruitment process.

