### Outcome measures

Outcome measures will be assessed by profession rehabilitation assessor, biochemical analyst and ultrasound doctor at baseline (T1) before intervention, 6 weeks (T2) and 12 weeks (T3) during intervention, and 3 months (T4) and 12 months (T5) during follow-up period. The demographic and clinical characteristics of the all participants will be collected at the time of enrollment.

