### Statistical analysis

All statistical analyses will be performed with IBM SPSS (Version 22.0, Chicago, IL, USA) by statisticians who are blinded to the group allocation. The outcomes analyses will be performed on an intention-to-treat basis. For the missing data, several sensitivity analyses will be conducted to evaluate their effects on the results. The Shapiro–Wilk will be used to test the normal distribution of the continuous variables for demographic and outcome measures. Continuous variables will be described as mean ± SD for normal distributions or median for non-normal distributions, categorical variables will be described as frequency. The χ^2^ test or Fisher’s exact test will be used to examine the comparisons between the four groups for categorical variables. When the normality of data distribution is found, two-way of variance with repeated measures will be applied to examine the main effects of the group and the time factor and group-time interaction effects. A simple effect post hoc analysis will be conducted, when time-group interaction is significant. Additionally, if homogeneity is not found, a linear mixed model will be adjusted for gender and KL grade. To mitigate bias and potential confounding variables, the propensity score matching (PSM) method will be employed [50]. Significant level for all tests will be set at 0.05 for all statistical tests and corrected for multiple comparisons using the Bonferroni-adjusted method, and 95% confidence interval will be reported.

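### The main analysis appears to count baseline as an outcome visit and adjusts for the stratification factors only if an undefined check fails, which wastes precision and dilutes the group main effect

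*Protocol article*

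**What the plan says.** Under Statistical analysis the main model for normally distributed outcomes is a two-way repeated-measures ANOVA that tests group, time and their interaction. No covariate is named. The next step is conditional: "A simple effect post hoc analysis will be conducted, when time-group interaction is significant". Adjustment for the stratification factors is conditional as well: "Additionally, if homogeneity is not found, a linear mixed model will be adjusted for gender and KL grade". The article does not say whether homogeneity means equal variances, sphericity or balance at baseline, and this fallback names no baseline covariate either.

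The allocation method is stated in the section on randomization and concealment: "The stratified randomization with gender and KL grade as factors will be used to randomly assign the eligible participants to four groups".

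Under Outcome measures, assessments take place "at baseline (T1) before intervention, 6 weeks (T2) and 12 weeks (T3) during intervention", with T4 and T5 falling after treatment has ended.

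Under Sample size, the between-factor test of a repeated-measures ANOVA is powered with "number of groups 4, number of measures 5"; the effect size entered is f = 0.25, at alpha 0.05 and 80% power, and the result is 168.

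**The concern.** Only five assessments are scheduled, and the first precedes treatment. A count of five measures is reached only by including it, so T1 appears to be a level of the time factor. The Statistical analysis section does not list the levels, so this is an inference, though no other reading fits the two sections together.

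Three things follow.

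- Randomization makes the expected group difference at T1 zero. A group main effect averaged over T1 to T5 mixes that zero with the four visits at which treatment can act.
- Baseline WOMAC, likely to be a strong predictor of later WOMAC, is used as an outcome and not to remove variance.
- The trial stratifies by gender and KL grade, but its main model ignores both unless an unspecified check on the data fails. The model is therefore not fixed in advance.

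At stake are the power and readability of the comparisons behind Aims 1 to 3 (D against B or C, B against C, B against A).

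**Working it through.** **Inputs from the article.** Four groups, m = 5 measures, f = 0.25, alpha 0.05, 168 before drop-out.

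**Assumptions, not in the article.** Within-patient correlation r, shown from 0.3 to 0.9; compound symmetry; the same group difference at T2, T3, T4 and T5; no difference at T1; no Bonferroni correction in the power figures.

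**1. The plan's own figure.** For the between factor, lambda = f² × N × m / (1 + (m − 1)r), with 3 and N − 4 degrees of freedom. At r = 0.9, lambda = 0.0625 × 168 × 5 / 4.6 = 11.4 and power is 0.81. With N in steps of 4, 168 is returned exactly at r = 0.90 to 0.92; at r = 0.5 the answer is 112. So 168 is reproducible, but only at a high correlation that the article does not state. The drop-out step also reproduces: 168 / 0.8 = 210, rounded up to 53 per group, gives 212.

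**2. Dilution.** With difference d at four visits and 0 at T1, the five-visit average is (0 + 4d)/5 = 0.80d, whatever r is. A simulation of 4,000 trials at r = 0.5 gave 0.40 against a true 0.50.

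**3. Information per unit of squared post-baseline effect.**

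- Five-visit group main effect: 0.64 / ((1 + 4r)/5)
- Baseline-adjusted mean of T2 to T5: 1 / ((1 + 3r)/4 − r²)

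| r | Main effect | Baseline-adjusted | Ratio |
|---|---|---|---|
| 0.3 | 1.455 | 2.597 | 1.79 |
| 0.5 | 1.067 | 2.667 | 2.50 |
| 0.7 | 0.842 | 3.509 | 4.17 |

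**4. Power at 168 completers, f = 0.25 at the post-baseline visits.** For the main effect and the adjusted mean, lambda = 168 × 0.0625 × information = 10.5 × information. For the group-by-time interaction, lambda = 168 × 0.0625 × 0.8 / (1 − r), with 12 and 4 × 164 = 656 degrees of freedom. The factor 0.8 is the squared deviation of the profile (0, 1, 1, 1, 1) from its mean: 0.64 + 4 × 0.04.

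| r | Main effect, 5 visits | Interaction, 12 df | Baseline-adjusted mean, T2–T5 |
|---|---|---|---|
| 0.3 | 0.92 | 0.59 | 0.996 |
| 0.5 | 0.80 | 0.78 | 0.996 |
| 0.7 | 0.69 | 0.96 | >0.999 |
| 0.9 | 0.60 | >0.99 | >0.999 |

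The simulation at r = 0.5 gave 0.798 for the main effect and 0.995 for the adjusted mean.

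**5. Comparisons at a single visit.** Baseline adjustment multiplies the variance by 1 − r²: 0.91, 0.75 and 0.51 at r = 0.3, 0.5 and 0.7.

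**6. Omitting the strata.** If gender and KL grade explain a share R² of the variance, standard errors are too large by 1/√(1 − R²): 1.010 at R² = 0.02 and 1.054 at R² = 0.10. At R² = 0.10 the actual two-sided error at nominal 0.05 is 2 × (1 − Φ(1.96 × 1.054)) = 0.039. The article gives no R².

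**The case against.** A reader might infer that the trial's primary estimate is biased toward zero. The article does not support that. It nowhere names the group main effect as the primary estimate; it lists that effect beside the time effect and the interaction. With T1 as a level, the interaction is the usual test of differential change, and the simple effects compare groups visit by visit. Neither is diluted, and the simple effects can supply the contrasts in the aims. Keeping baseline as a repeated level is conventional and valid, though less efficient. This part of the objection stands and confines the dilution to one test, albeit the one used for sample size.

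It can also be said that the interaction route is adequate. At a correlation near 0.9, which the stated 168 implies, interaction power exceeds 0.99. That is right, but at 0.3 it is 0.59, and the article does not power this test although it gates the simple effects.

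The entered f = 0.25 may already describe the five-visit average. The dilution would then be inside it, and the main-effect shortfall in step 4 would not arise. The article does not say which is meant.

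The loss from omitting the strata is small, rests on an assumed R² and errs on the conservative side. This stands.

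Finally, covariate detail is often left to an analysis plan. Here, however, the article itself names the model and makes the adjustment conditional, so the point concerns what is written.

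**Conclusion.** The point holds as one of efficiency and prespecification: it should be fixed, but it does not undermine the trial. No inflated false-positive rate and no invalid inference has been shown.

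The group main effect captures 0.80 of a constant post-baseline difference. Depending on correlation, the baseline-adjusted analysis carries 1.79 to 4.17 times its information over r = 0.3 to 0.7. The interaction and per-visit comparisons escape dilution but forgo the same adjustment, and a 12-degree-of-freedom test stands in front of the per-visit comparisons. Leaving out gender and KL grade does not bias the estimate; it makes standard errors about 1% to 5% too large for R² of 0.02 to 0.10.

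These sizes rest on T1 being a level of time (inferred), compound symmetry, a constant effect from T2 to T5, and f = 0.25 describing the post-baseline visits. Nor should the reader conclude that 168 is wrong: it is reproducible at a high correlation that is simply not stated.

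**What to change.** Prespecify one linear mixed model with T2 to T5 as the outcome visits. Its fixed effects should be group, visit, group-by-visit, baseline value, baseline-by-visit, gender and KL grade, and its use should not depend on any check of the data. Report the contrasts for Aims 1 to 3 at each post-baseline visit and averaged over those visits, without making them conditional on a significant interaction. A constrained model that keeps T1 as an outcome but gives all groups a common baseline mean would also serve.

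The cost is small. Baseline assessments are completed before the allocation envelope is opened, and both stratification factors are known at randomization, so no new data, visits or patients are needed. Beyond rewording, the sample-size basis must be restated for the new test. It should give the assumed correlation and say whether f = 0.25 refers to the post-baseline visits or to the average over all five.

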## Methods/Design

### Study design

This protocol will be a placebo-controlled, assessor-blinded randomized trial, which will be included 12-week intervention and 1-year follow-up. This protocol will be conducted in accordance with the Standard Protocol Items: Recommendations for Interventional Trials (SPIRIT) [25]. A total of 212 patients diagnosed with KOA will be randomly and equally assigned into the group A (IAI-placebo), group B (IAI-PRP), group C (TC + IAI-placebo), and group D (TC + IAI-PRP). A brief flowchart of the entire study is shown in Fig. 1, and the schedule of events is provided in Table 1. The study protocol was approved by the Ethics Committee of Shanghai Seventh People’s Hospital (2022-7th-HIRB-067) and registered in the Chinese Clinical Trial Registry (ChiCTR2300067559).

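### Propensity score matching is committed to without condition beside an intention-to-treat analysis of a randomised trial, and its role is not defined

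*Protocol article*

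**What the plan says.** The Statistical analysis section fixes the analysis principle: "The outcomes analyses will be performed on an intention-to-treat basis". It then names a repeated-measures ANOVA with group, time and their interaction, and gives a fallback: "if homogeneity is not found, a linear mixed model will be adjusted for gender and KL grade". The next sentence is "To mitigate bias and potential confounding variables, the propensity score matching (PSM) method will be employed". It carries no condition and is not called a sensitivity, exploratory or per-protocol analysis. The paragraph does speak of sensitivity analyses, but only for missing data.

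On allocation, the randomisation section says: "The stratified randomization with gender and KL grade as factors will be used to randomly assign the eligible participants to four groups". Assignment is by sealed opaque envelopes, opened after the baseline assessments, and the Study design section describes equal allocation of 212 patients to the four arms.

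The Sample size section gives "effect size 0.25, alpha 0.05, power 0.80, number of groups 4, number of measures 5, and the sample size is calculated as 168", and then, for a "20% drop-out rate, the final sample size will therefore be 53 in each group, with a total of 212 subjects". It makes no other allowance for patients who leave the analysis.

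**The concern.** Propensity score matching was devised for comparisons in which patients were not allocated by chance. Here they were. The true probability of each arm is fixed by design, and an estimated propensity score can only describe chance imbalance, which the ordinary standard error already allows for. The usual form of the method then keeps the patients who have a close counterpart in the other arm and sets the rest aside.

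Two things are at stake if the matched set feeds the outcome analysis. First, the result would come from a subset of those randomised, although the paragraph promises an analysis of all of them. Conventional matching is also a two-group method, and the aims are pairwise (D against B or C, B against C, B against A). Each contrast could therefore rest on a different subset. Second, precision would fall in a trial with almost no spare patients. Because the role of the matching is not stated, a reader of the eventual report could not tell from this plan which set the WOMAC result was meant to come from.

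**Working it through.** **1. The plan's own figure.** Inputs from the Sample size section: 168 evaluable patients, 20% drop-out, four arms.

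168 / (1 − 0.20) = 210; 210 / 4 = 52.5, rounded up to 53 per arm; 53 × 4 = 212. The stated total reproduces. The surplus is 212 − 210 = 2 patients, so there is no room for a further loss.

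**2. The basis of 168.** For the between-group test of a repeated-measures ANOVA, the noncentrality is λ = f²·N·m / (1 + (m − 1)ρ), with 3 and N − 4 degrees of freedom, f = 0.25 and m = 5. The correlation ρ between visits is not stated. A ρ of 0.5 requires 112 patients, 0.8 requires 152 and 0.9 requires 168. At N = 168, power is exactly 0.80 when ρ is about 0.926: λ = 0.0625 × 168 × 5 / (1 + 4 × 0.926) = 52.5 / 4.704 = 11.16. The missing correlation is not the point here, so results are shown for ρ = 0.926 and ρ = 0.5.

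**3. How many patients matching might keep.** The article gives no algorithm, so every input in this step is an assumption: two randomised arms, independent standard-normal baseline covariates, a logistic propensity score, greedy 1:1 matching, and a caliper of 0.2 SD of the logit. The table gives the mean share kept; the ranges reflect separate simulation runs.

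| Covariates | 53 per arm | 42 per arm |
|---|---|---|
| 4 | 75% | 72% |
| 6 | 74% | 70% |
| 8 | 71–72% | 67–68% |

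The arms differed only by chance in these simulations. Keeping 70–75% of 53 leaves about 37 to 40 patients per arm (53 × 0.70 = 37.1; 53 × 0.75 = 39.8). Other things equal, the standard error of a pairwise difference grows by 1/√0.75 = 1.15 to 1/√0.70 = 1.20, that is by 15–20%.

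**4. What a loss would do to power.** This is the formula of step 2 at reduced N. For a 30% loss, N = 118 and λ = 0.0625 × 118 × 5 / 4.704 = 36.875 / 4.704 = 7.84 at ρ = 0.926.

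| Unmatched share of 168 | N left | Power, ρ = 0.926 | Power, ρ = 0.5 |
|---|---|---|---|
| 0% | 168 | 0.80 | 0.95 |
| 10% | 151 | 0.75 | 0.92 |
| 20% | 134 | 0.69 | 0.89 |
| 30% | 118 | 0.63 | 0.84 |
| 50% | 84 | 0.47 | 0.67 |

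This spreads the loss evenly over the four arms and gives no credit for closer balance after matching. It is at the unadjusted 0.05 level.

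**The case against.** The strongest reply is that the outcome analysis is already named. It is the repeated-measures ANOVA or the mixed model, on an intention-to-treat basis, and the matching sentence comes later and does not say that it defines the analysis set. An intention-to-treat ANOVA and a supplementary matched analysis can stand side by side. This reply holds in part. A reader might infer that the primary WOMAC result will come from matched patients, and that the plan therefore flatly contradicts itself. The text does not say so. What it does is commit to the method without giving it a place, so the conflict is conditional on use.

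A reader might also infer that randomised patients will certainly be discarded. That too is not stated. Full matching or weighting could keep everyone. The word used is matching, however, and nothing points to a variant that retains all patients. Such a variant would still aim at allocation confounding that randomisation has removed.

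Covariates, caliper and algorithm may well be left to an analysis plan that is not shown, and their absence is no fault here. But such detail would not cure an unconditional commitment to the method.

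Finally, bias can arise after randomisation: 20% drop-out is expected, and Tai Chi cannot be blinded. The aim of mitigating bias is therefore not empty. But the article does not tie matching to drop-out, since missing data have their own sentence, and matching on baseline characteristics cannot correct for participants knowing that they do Tai Chi. It should also be granted that matching on baseline variables has not been shown to bias this trial. The expected cost is precision and a changed target population.

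**Conclusion.** The point holds in a conditional form. The article commits without qualification to a method that a randomised comparison does not need, and does not say how it relates to the declared intention-to-treat analysis. If the matching feeds the outcome analysis in its usual form, the analysed set is no longer the randomised set, and the sample size has no allowance for the loss.

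The size is illustrative. About 70–75% of two 53-patient arms would be kept under the assumed 1:1 greedy scheme with 4 to 8 covariates. A 30% loss from 168 would take power from 0.80 to about 0.63, or from 0.95 to 0.84 if the correlation between visits is 0.5. These figures rest on an assumed algorithm, assumed independent covariates and an unstated correlation. The conclusion itself rests only on the wording of the analysis paragraph and on the randomised design.

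**What to change.** Delete the matching sentence. At minimum, label it an exploratory analysis, reported beside the intention-to-treat result and unable to replace it.

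Handle chance imbalance by covariate adjustment in all randomised patients, analysed as allocated: gender and KL grade, which the plan's mixed model already uses, plus the baseline value of the outcome.

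Deleting or labelling the sentence is a one-line change with no effect on data collection or patient numbers. The covariate adjustment asks for somewhat more rewording. The adjusted mixed model would be used without waiting for a homogeneity check, and T1 would become a covariate rather than one of the five repeated outcomes. The sample-size text should then refer to four post-baseline measures. Before any credit for baseline adjustment, the noncentrality at N = 168 hardly moves: 0.0625 × 168 × 4 / (1 + 3 × 0.926) = 42 / 3.778 = 11.12, against 11.16 with five measures. At a correlation of 0.5 it is 42 / 2.5 = 16.8, against 52.5 / 3 = 17.5.

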**Methods:**

This study protocol will be a placebo-controlled, assessor-blinded randomized trial involving 12-week intervention and 1-year follow-up. The stratified randomization will be used to randomly assign the 212 participants to four groups: group A (placebo IAI); group B (PRP IAI); group C (TC and placebo IAI); group D (TC and PRP IAI). Injection will be performed once a week, three consecutive times as a course, after a week of rest to continue the next course, a total of 3 courses (12 week). Additionally, the TC interventions will be carried out 3 days per week for a total of 12 weeks. The primary outcome measures will include the efficacy (Western Ontario and McMaster Universities Osteoarthritis Index), acceptability and safety of these interventions. The secondary outcome measures will include physical function (Timed Up and Go test), walking function (Gait Analysis), inflammatory factor levels (e.g., Interleukin-1 β, interleukin-6, vascular endothelial growth factor), quality of life (36-Item Short Form Health Survey), volume of patellofemoral cartilage and effusion-synovitis (MRI). Two-way of variance with repeated measures will be applied to examine the main effects of the group and the time factor and group-time interaction effects for all outcome measures.

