Therefore, the placebo-controlled, assessor-blinded randomized trial will be design in the present protocol, which will include group A (IAI-placebo), group B (IAI-PRP), group C (TC + IAI-placebo), and group D (TC + IAI-PRP). This protocol will allow to be achieve the study purpose as follows:

Aim 1: To examine the effectiveness and safety of combined IAI-PRP and TC for KOA treatment by comparing the group D vs B or C.

Aim 2: To compare the differences of efficacy between the IAI-PRP and TC in the KOA treatment by comparing the group B and C.

Aim 3: To provide high-quality evidence of PRP for KOA treatment by comparing the group B and A.

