### Primary outcomes

Efficacy: The Western Ontario and McMaster Universities Osteoarthritis Index (WOMAC) will be used to evaluate the score of the pain, stiffness and daily functional activities of the participants. A number of studies demonstrated that the WOMAC is a reliable and valid instrument for evaluating the joint function of KOA [36, 37]. The aggregate score of the WOMAC is 96, which mainly includes pain (20 points), stiffness (8 points) and daily functional activities (68 points). The higher the score is, the more serious the knee joint dysfunction is. In addition, the anchor-based method will be utilized to determine the minimal clinically important difference (MCID) in order to evaluate the clinical significance of the changes in WOMAC [38]. All patients will be asked to rate their knee improvement compared to baseline at 3 and 12 months. The question will be: “How is your health today compared with baseline?” Patients will be able to choose from five Likert response options: “a great deal better,” “somewhat better,” “equal,” “somewhat worse,” and “a great deal worse.” The MCID will be determined by calculating the average change score for patients who reported their knee improvement as “somewhat better” in the transitional question. This will involve subtracting the baseline scores from the scores at 3 and 12 months during the follow-up period. The MCID proportion (MCID%) will be calculated as the percentage of the sample with a change in scores that surpasses the MCID threshold.Acceptability: The acceptability is an important part of the evaluation of intervention. The rate of referral, retention and drop-out will be used to comprehensively evaluate the acceptability of interventions. • Referral rate is defined as the ratio of the number of referrals made by different departments and hospitals to all participants (T1); • Retention rate is the ratio of the number of participants who completed the study (T5) to all participants (T1); • Drop-out rate is the ratio of the number of participants who dropped out after randomization to all participants (T1), talk with the drop-out participants to identify their reasons for dropping out.Safety: The occur rate of adverse events is defined as the ratio of the number of occurred participants to all participants (T1), which will be used to evaluate the safety of intervention. During the intervention and follow-up, the adverse events (e.g., pain, fall) will be recorded on the Case Report Form (CRF) by the way of the monitor and self-report, and will be evaluated for relevance to the intervention.

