We recognize this study also has limitations. This research has an inevitable limitation associated with the difficulty in controlling the methodology of blinding during the TC intervention, which cannot be blinded for the participants and therapists due to the visible of the TC intervention. Although the outcome assessors and data analyzer will be blinded to the group allocation, which might increase the risk of detection bias during the study’s implementation. Additionally, the PRP preparation and injection need to be operated by medical personnel in medical institutions, which may limit the promotion and application of the combined IAI-PRP and TC in the community and home.

In summary, the results of the study protocol will demonstrate that the efficacy, acceptability and safety of the combined IAI-PRP and TC for treatment of KOA. This method may have a potential opportunity to treat KOA. The study protocol will provide guide significance in integrate exist and different rehabilitation technology and design more effective rehabilitation program for KOA.

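### Safety of the combination is a primary outcome judged by D vs B or C, but the stated test is a four-group difference test with Bonferroni-corrected follow-up, which cannot support a demonstration of safety

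*Protocol article*

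**What the plan says.** The abstract of the protocol article puts safety among the primary outcomes: "The primary outcome measures will include the efficacy (Western Ontario and McMaster Universities Osteoarthritis Index), acceptability and safety of these interventions". Under Primary outcomes, safety becomes a proportion: "The occur rate of adverse events is defined as the ratio of the number of occurred participants to all participants (T1"). Aim 1, at the end of the Background, names the contrasts: "To examine the effectiveness and safety of combined IAI-PRP and TC for KOA treatment by comparing the group D vs B or C".

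For a proportion, the Statistical analysis section offers one inferential method. A chi-square or Fisher test "will be used to examine the comparisons between the four groups for categorical variables". On error control it says: "Significant level for all tests will be set at 0.05 for all statistical tests and corrected for multiple comparisons using the Bonferroni-adjusted method". The same sentence promises 95% confidence intervals, but nothing links them to the conclusion on safety.

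The last paragraph of the Discussion announces that "the results of the study protocol will demonstrate that the efficacy, acceptability and safety of the combined IAI-PRP and TC". The first paragraph of the Discussion is milder and says only that safety will be explored.

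**The concern.** Three statements do not fit together.

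- **Test and aim.** A four-group test asks whether any of four proportions differ. Aim 1 asks whether D exceeds B, and whether D exceeds C. The four-group result answers neither.
- **Correction and purpose.** Bonferroni limits false claims of a difference. With harms, the costly error is to overlook a real excess. Each added comparison lowers the threshold and makes that error more likely. The rule is written for all tests and makes no exception for adverse events.
- **Evidence and claim.** A difference test can show a difference. It cannot show that there is none of importance. The article nevertheless announces a demonstration of safety and gives no criterion that could support one.

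What is at stake is a primary conclusion. A trial sized on another outcome could find no significant difference in adverse events, and that result would sit beside a claim of safety announced in advance.

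**Working it through.** **Inputs from the article.** 53 per group, 212 in total; alpha 0.05; Bonferroni; denominator all participants at T1, so 53 per group are used throughout.

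**Inputs assumed.** Two-sided tests, independent groups, and comparator adverse-event rates of 5% to 30%, each doubled in D. The article gives no rate. The number of comparisons is not fixed either: Aim 1 implies 2, and all pairs of four groups give 6.

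**The plan's own figure.** 168/(1 − 0.20) = 210; 210/4 = 52.5, rounded up to 53; 4 × 53 = 212. This reproduces. The 168 rests on an ANOVA effect size of 0.25, so adverse events played no part in the sample size.

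**Pairwise power, worked for 10% vs 20%.** By the normal approximation, power = Φ[(δ − z·SE0)/SE1], with
- δ = 0.10
- SE0 = √(2 × 0.15 × 0.85/53) = 0.0694
- SE1 = √((0.10 × 0.90 + 0.20 × 0.80)/53) = 0.0687

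Results:
- alpha 0.05, z = 1.960: (0.10 − 0.1360)/0.0687 = −0.52; power 0.30, missed 70%
- alpha 0.05/2, z = 2.241: (0.10 − 0.1555)/0.0687 = −0.81; power 0.21, missed 79%
- alpha 0.05/6, z = 2.638: (0.10 − 0.1830)/0.0687 = −1.21; power 0.11, missed 89%

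Exact enumeration of the uncorrected chi-square test gives the same rounded values (70%, 79%, 89%). Fisher's test misses more: 79%, 85% and 93%.

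**Chance of missing a doubling in D, 53 per group.** Pairwise columns are exact chi-square. The four-group column is simulated (200,000 runs) with A, B and C at the comparator rate.

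| Comparator → D | Four-group, 0.05 | Pairwise, 0.05 | Pairwise, 0.05/2 | Pairwise, 0.05/6 |
|---|---|---|---|---|
| 5% → 10% | 84% | 85% | 92% | 96% |
| 10% → 20% | 69% | 70% | 79% | 89% |
| 15% → 30% | 51% | 53% | 65% | 79% |
| 20% → 40% | 34% | 37% | 48% | 64% |
| 30% → 60% | 8% | 12% | 18% | 31% |

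**The four-group test does not isolate the aim.** If the rate doubled from 10% to 20% in both B and D, the four-group test would miss this 63.5% of the time and so reject 36.5% of the time, although D − B would be zero.

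**What 53 per group can exclude.** With equal observed rates p, the 95% half-width for a risk difference is 1.96 × √(2p(1 − p)/53). At p = 0.10 this is 1.96 × √(0.18/53) = 0.114, about 11 percentage points. At 5% it is about 8 points and at 20% about 15. Two groups with identical 10% rates would thus still leave an excess of about 11 points open.

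**Size needed.** For 80% power at 10% vs 20%, n per group = (1.960 × √0.255 + 0.842 × √0.25)²/0.10² ≈ 199 at 0.05. It rises to 242 at 0.05/2 and 308 at 0.05/6.

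**The case against.** The strongest reply is that nowhere does the article say a non-significant result will be taken as proof of safety. That is correct. A reader might infer such a rule from the closing sentence, but the text does not contain it. Aim 1 speaks of examining safety, and the Dissemination plans promise to publish negative results too. What stands is narrower: the closing sentence promises a demonstration that the stated test cannot deliver.

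Second, a reader might conclude that Bonferroni shrinks the threshold of the four-group test itself. That test is a single test, and the correction most naturally bears on pairwise follow-up. The four-group figures above are therefore at 0.05.

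Third, a reader might take 70–90% as the general miss rate for a doubled harm. It belongs only to an assumed 10% vs 20%. Pain counts as an adverse event and follow-up lasts a year, so the true rate may be higher and the problem smaller.

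Fourth, the article has other safeguards: confidence intervals, an assessment of whether events relate to the intervention, and review of serious events by an independent board. These soften the concern. They do not supply the D vs B or D vs C comparison, and they do not lift the correction from harms.

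Finally, a harm margin and an interval method may stand in an analysis plan that is not shown. Their absence is not held against the article. The blanket correction and the closing claim are its own statements.

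**Conclusion.** The point holds in this limited form. For a primary safety outcome, the stated test does not match the contrasts in Aim 1, the blanket correction lowers the chance of seeing harm in those contrasts, and the wording of the Discussion goes beyond what a difference test can show.

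The size depends on an adverse-event rate that the article does not give. Pairwise, from no correction to six comparisons, a doubling is missed 85–96% of the time at a 5% comparator rate, 70–89% at 10%, 37–64% at 20% and 12–31% at 30%. These figures assume two-sided chi-square tests and 53 analysed per group.

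Low power for adverse events is usual in a trial sized on efficacy and is not in itself the fault. A reader might extend the point to retention and drop-out. The documents do not support that, since no aim claims that the groups are equivalent on them.

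**What to change.** In the Statistical analysis section:
1. State that adverse-event comparisons are exempt from the Bonferroni correction.
2. Base the safety comparison on the risk differences D − B and D − C, with B − A for PRP alone, each with an unadjusted 95% confidence interval.
3. Report for each the largest excess that the interval does not exclude.

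In the last paragraph of the Discussion, replace the promise to demonstrate safety. Say that adverse-event rates will be described with confidence limits and that a non-significant difference is not evidence of safety. A stronger statement is open to the sponsor only if it fixes a margin in advance and ties the claim to the upper limit.

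The cost is wording and a few intervals from data already collected, with no extra participants or visits. The downsides are a weaker safety claim than the one now announced and somewhat more chance differences flagged without the correction.
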